## Abstract

**Background:**

Endometriosis is a common benign condition, which is characterized by the growth of endometrial-like tissue in ectopic sites outside the uterus. Laparoscopic excision of the disease is frequently carried out for the treatment of severe endometriosis. Pelvic adhesions often develop following surgery and they can compromise the success of treatment. Ovarian suspension (elevating both ovaries to the anterior abdominal wall using a Prolene suture) is a simple procedure which has been used to facilitate ovarian retraction during surgery for severe pelvic endometriosis. The study aims to assess the effect of temporary ovarian suspension following laparoscopic surgery for severe pelvic endometriosis on the prevalence of post-operative ovarian adhesions.

**Methods:**

A prospective double blind randomised controlled trial for patients with severe pelvic endometriosis requiring extensive laparoscopic dissection with preservation of the uterus and ovaries. Severity of the disease and eligibility for inclusion will be confirmed at surgery. Patients unable to provide written consent, inability to tolerate a transvaginal ultrasound scan, unsuccessful surgeries or suffer complications leading to oophorectomies, bowel injuries or open surgery will be excluded.

Both ovaries are routinely suspended to the anterior abdominal wall during surgery. At the end of the operation, each participant will be randomised to having only one ovary suspended post-operatively. A new transabdominal suture will be reinserted to act as a placebo. Both sutures will be cut 36 to 48 hours after surgery before the woman is discharged home. Three months after surgery, all randomised patients will have a transvaginal ultrasound scan to assess for ovarian mobility. Both the patients and the person performing the scan will be blinded to the randomisation process.

The primary outcome is the prevalence of ovarian adhesions on ultrasound examination. Secondary outcomes are the presence, intensity and site of post-operative pain.

**Discussion:**

This controlled trial will provide evidence as to whether temporary ovarian suspension should be included into the routine surgical treatment of women with severe pelvic endometriosis.

**Trial registration:**

ISRCTN: ISRCTN24242218

## Background

Endometriosis is a common benign condition, which is characterized by the growth of endometrium-like tissue in ectopic sites outside the uterus. The condition is a significant cause of morbidity in women of the reproductive age [1]. Symptoms of endometriosis include dysmenorrhoea, dyspareunia, chronic pelvic pain and subfertility. The revised American Society for Reproductive Medicine (ARSM) classification is the most widely accepted staging system for endometriosis, where a score is used to grade the disease as absent (0), minimal (1-5), mild (6-15), moderate (16-40) or severe (> 40) [2].

Surgical excision of the disease is frequently carried out for the treatment of severe endometriosis. Laparoscopic approach to surgery provides superior views of the pelvis and facilitates complete excision of endometriotic lesions [3]. Although laparoscopic surgery is considered to be less traumatic to pelvic tissues than open surgery, a significant number of women develop post-operative pelvic adhesions even after this form of surgery. The most common site of post-operative adhesions formation is the ovary [4]. Formation of severe post-operative adhesions can compromise the success of surgery for endometriosis by causing chronic pelvic pain, infertility, dysparaeunia and intestinal obstruction [5]. Adhesions formation after laparoscopic endometriosis surgery has been reported in the range of 50 to 100 percent [5-8].

The high incidence of post-operative adhesions in endometriosis patients and their clinical significance underlines the importance of modifying surgical techniques in order to reduce potential adhesion formation. Intra-peritoneal administration of anti-adhesive solutions (e.g. icodextrin, hyaluronic acid) and drugs (e.g. steroids, heparin) at the time of surgery has been advocated as a way of reducing the incidence of post operative adhesions. Currently, only anti-adhesive fluids containing hyaluronic acid have showed evidence of reduction of adhesions however, more studies will be needed to confirm this [9]. Adjuvants have also been suggested to further improve the adhesion reduction, however to date, the most effective product for prevention of postoperative adhesion is yet to be discovered [10].

### Ovarian suspension

Ovarian suspension is a simple procedure which has been used to facilitate ovarian retraction during surgery for severe pelvic endometriosis without any reported complications [11]. A study by Abuzeid et al. showed that temporary ovarian suspension following surgery for severe endometriosis may lead to a reduction in post-operative adhesions [12]. A small retrospective study also found significant reductions in the number of women with post-operative adhesions following ovarian suspension in comparison with data from the literature [13].

### Objective

The aim of this study is to assess the effect of temporary ovarian suspension following laparoscopic surgery for severe pelvic endometriosis on the prevalence of post-operative ovarian adhesions.

## Methods

This is a prospective double blind randomised controlled trial which will be conducted at the University College London Hospital Endometriosis Centre. This centre is a tertiary referral unit for women with severe pelvic endometriosis and receives patients from a wide area of south east England.

### Inclusion criteria

Women age 19 years or older who are diagnosed with severe pelvic endometriosis on pre-operative transvaginal ultrasound scan would be invited to join the study. Suitability for randomisation will be determined at surgery. Only women with severe endometriosis requiring extensive dissection of both pelvic side walls and/or rectovaginal space with preservation of the ovaries and uterus will be included in the study.

Exclusion criteria are inability or unwillingness to provide written consent, inability to tolerate a transvaginal ultrasound scan, unsuccessful surgeries and in cases of complications such as unplanned oophorectomies, bowel injuries or conversions to open surgery.

### Interventions

During laparoscopic treatment for severe endometriosis, both ovaries are routinely suspended to the anterior abdominal wall using a Prolene suture, which is brought out onto the skin and secured using a fine haemostat or 'mosquito' clip during surgery. This is performed to facilitate access to the pelvic side walls during surgery and a complete excision of the disease.

At the end of the operation, women will be randomised to have one ovary suspended for 36 to 48 hours post-operatively. One of the two ovarian suspension sutures will be cut to allow that ovary to fall back into the lesser pelvis. A new transabdominal suture will be reinserted at the same site to act as a placebo. The pneumoperitoneum will then be deflated and the Prolene stitch of the suspended ovary will be tightened with a surgical knot placed over the skin to secure the ovary to the abdominal wall. This will ensure that the suspended ovary is lifted as far away from the pelvis as possible. The surgical knots will be secured with the space of a Carless scissor between the skin and the knot to allow easier removal of the suture and reduce patient discomfort. All randomized patients will therefore have two abdominal sutures of similar length and both the patient and clinical staff - apart from the surgical team - will be blinded to the randomisation process.

A label will be attached to the operation notes to define a) the randomisation number b) the operation date and time and c) the time to remove the sutures. There will be no documentation of the randomisation site in the operation notes.

Both sutures will be cut 36 to 48 hours after surgery by a ward nurse who will not be part of the study and will be blinded to the ovarian suspension site. The only members of staff who will be aware of the site of ovarian suspension will be the surgeons who will be under strict instructions not to discuss individual patient's treatment allocations with the patient or any other members of the clinical and nursing staff.

### Randomisation

Participants will be randomised to unilateral suspension of either the right or left ovary. Block randomisation will be used with three varying block sizes of minimum size 4. The randomisation schedule will be produced by our statistician using the external Stata command *ralloc.*

When a participant is recruited to the trial, consecutive randomisation envelopes will be opened and the principal surgeon will be told which ovary to suspend. Only the patient's randomisation number will be recorded in the patient's operation notes. No other member of staff will be aware of women's treatment allocations.

At the end of the study, the randomisation will be unblinded for analysis and details of the ovarian suspension will be added to each patient's record.

### Incident Reporting & unblinding procedure

Adverse events will be recorded from the time of ovarian suspension until three months after surgery when the suspension results can be determined. The principal investigator will be responsible for the reporting of all serious adverse events (SAE) or suspected unexpected serious adverse reactions (SUSAR) immediately as the trial personnel become aware of an event to the chief investigator. The chief investigator should report all fatal or life-threatening events as soon as possible to the joint biomedical research unit (JBRU). This needs to be done not later than seven days after the chief investigator was first aware of the reaction. All events which are not fatal or life-threatening are also reported as soon as possible and not later than 15 days after the chief investigator was first aware of the reaction. The research and ethics committee (REA) also requires a report of all SAEs and SUSARs. The principal investigator will also follow all SAEs and SUSARs through to outcome.

In cases where patients experience SUSAR, both suspension sutures will be cut and the randomisation process will be unblinded by contacting the principal investigator or the ward sister who has a sealed randomisation envelope.

### Ethical considerations

Approval for this study was obtained from the Medical Ethical Committees of the University College Hospital, London, UK. In each patient fulfilling the inclusion criteria, written informed consent is obtained before randomisation. Women refusing participation are registered.

#### Follow-up

Three months after ovarian suspension, all patients in the study will be invited for a transvaginal ultrasound scan to assess ovarian mobility (Figure 1). Ovarian adhesions will be diagnosed in women with evidence of restricted ovarian mobility on targeted palpation using transvaginal ultrasound probe [14]. The ultrasound operators will be blinded to the details of the operative procedure and women's randomisation allocation.

**Figure 1 F1:**
[figure not shown]
**Flowchart of ovarian suspension study**.

#### Outcome measures

##### Primary outcome measure

The primary outcome is the prevalence of ovarian adhesion on ultrasound after surgery. The presence of ovarian adhesions will be assessed by a combination of gentle pressure with the vaginal probe and abdominal pressure with the examiners free hand as in a bimanual examination. The presence of ovarian adhesions will be diagnosed when the ovarian mobility is restricted and the ovary cannot be separated from the peritoneum of the lateral pelvic wall and/or pouch of Douglas.

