## Discussion

Ovarian adhesions after surgery for pelvic endometriosis are common problems with its associated morbidity. Numerous adhesion prevention strategies, mostly based on microsurgical principles, have been reported. These include minimalising tissue trauma, meticulous hemostasis, irrigation and the use of low reactive sutures. Suspending the ovaries post-operatively has been suggested as an easy and possibly effective way of reducing ovarian adhesions. To the best of our knowledge, a larger prospective study has not been done to evaluate this. Our randomised controlled trial will provide evidence as to whether this simple surgical procedure should be included into the routine surgical treatment of women with severe pelvic endometriosis.

There is a potential risk of injury to the bowels and blood vessels during insertion of the suspension sutures. However, the chance of this occurring is likely to be very small. There has also been no reported complication as a result of ovarian suspension in previous studies.

The original study protocol was to perform a diagnostic laparoscopy to assess for ovarian adhesions three months after surgical treatment for endometriosis. However, due to problems with patient recruitment, the study protocol was modified to the current study.

Traditionally, post-operative adhesions can only be assessed by laparoscopy, but recent studies have shown that targeted palpation with ultrasound probe could be used as an alternative method to diagnose adhesion. Guerriero et al. found that the fixation of the ovary to the uterus evaluated by transvaginal ultrasonography, had a good specificity (86%) and high positive predictive value (PPV) of 81% [16]. More recently, Okaro et al. found good correlation between ovarian mobility on transvaginal ultrasound and at laparoscopy (kappa 0.81) [17]. These positive results were also shared by Holland et al [14]. Transvaginal ultrasound has proven to be an indispensible, non-invasive and inexpensive way of assessing ovarian adhesion.

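### The primary outcome counts ovarian adhesions at only two pelvic sites, so an ovary fixed solely to the anterior abdominal wall, where only the suspended ovary is held, would score as adhesion-free

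*Protocol article*

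**What the plan says.** The Objective is the effect of temporary suspension "on the prevalence of post-operative ovarian adhesions". It names no anatomical site.

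The article describes the diagnosis of adhesion twice:

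- Follow-up: "Ovarian adhesions will be diagnosed in women with evidence of restricted ovarian mobility on targeted palpation using transvaginal ultrasound probe". Restricted mobility is enough, and no site is named.
- Primary outcome measure: adhesion requires restricted mobility and also that "the ovary cannot be separated from the peritoneum of the lateral pelvic wall and/or pouch of Douglas". Both conditions must hold, and only two sites count.

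Statistical analysis refers only to the presence of ovarian adhesions at three months, as paired binary data, and does not choose between the two descriptions.

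Interventions fixes where each ovary lies after surgery. The suspended ovary's stitch is "tightened with a surgical knot placed over the skin to secure the ovary to the abdominal wall", and "This will ensure that the suspended ovary is lifted as far away from the pelvis as possible". For the control ovary, "One of the two ovarian suspension sutures will be cut to allow that ovary to fall back into the lesser pelvis". Both sutures are cut at 36 to 48 hours.

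**The concern.** An ovary with restricted mobility that is fixed only to the anterior abdominal wall is positive under the Follow-up wording and negative under the Primary outcome wording. The second section carries the formal definition, so its literal reading governs: that ovary scores as a success.

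The site rule is not neutral between the sides. It counts the region beside which the control ovary is left and omits the surface against which the suspended ovary is held. Blinding the ultrasound operator does not help, because the asymmetry lies in the scoring rule and not in the operator's judgement.

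At stake is whether the trial can tell preventing adhesions from moving them. The Discussion says the result will bear on whether suspension enters routine surgical treatment, and that question needs the distinction.

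**Working it through.** **1. The two rules by site of fixation (mobility restricted in every row)**

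| Ovary fixed only to | Follow-up rule | Primary outcome rule | Direction of any bias |
|---|---|---|---|
| Lateral pelvic wall or pouch of Douglas | adhesion | adhesion | none |
| Anterior abdominal wall | adhesion | no adhesion | favours suspension |
| Uterus, bowel or other ovary | adhesion | no adhesion | unknown |

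The third row has no known direction because the control ovary, back in the pelvis, may be as exposed to those structures as the suspended one, or more so.

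**2. The plan's own sample size**

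Inputs from Sample size: 60% adhesion per control ovary, a 50% reduction (to 30%), two-sided 5%, 80% power, independence within a woman. The paired formula is

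N = [1.96·√pd + 0.8416·√(pd − d²)]² / d²

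with p10 = 0.6 × 0.7 = 0.42, p01 = 0.4 × 0.3 = 0.12, pd = 0.54 and d = 0.30. This gives N = [1.96·√0.54 + 0.8416·√0.45]² / 0.09 = 44.66, so 45 women, and 45/0.9 = 50 recruited. Both stated figures reproduce and are not in dispute.

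**3. What the site rule could do**

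Assumptions, not in the documents:

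- True any-site adhesion is 60% on both sides, so suspension prevents nothing.
- A share q of suspended ovaries is fixed only at the anterior wall.
- No control ovary is lost to an uncounted site.

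The primary outcome rule then compares 60% with 60% − q. With n = 45 and independence (the plan's assumption), p10 = 0.6 × (0.4 + q), p01 = 0.4 × (0.6 − q), pd = p10 + p01 and d = q. The chance of a significant result favouring suspension is

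Φ{ [d·√45 − 1.96·√pd] / √(pd − d²) }

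| q | Counted rates | p10, p01 | Asymptotic | Exact McNemar |
|---|---|---|---|---|
| 0 | 60% v 60% | 0.24, 0.24 | 2.5% (nominal) | |
| 5 points | 60% v 55% | 0.27, 0.22 | 7% | 4% |
| 10 points | 60% v 50% | 0.30, 0.20 | 15% | 11% |
| 15 points | 60% v 45% | 0.33, 0.18 | 29% | 22% |
| 20 points | 60% v 40% | 0.36, 0.16 | 46% | 38% |

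For q = 10 points: [0.10 × 6.708 − 1.96 × √0.50] / √0.49 = (0.671 − 1.386)/0.70 = −1.02, and Φ(−1.02) = 0.15.

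**4. Sensitivity to loss on the control side**

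If 10 points of suspended and 5 points of control ovaries are fixed only at uncounted sites, the counted rates are 55% v 50% and false benefit is about 7%, not 15%. At 10 v 10 points the counted rates are equal and it returns to 2.5%.

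**The case against.** The strongest reply is that this is a matter of wording. The Follow-up sentence describes technique and the Primary outcome section gives the operational rule. The second is the first plus a site condition, which is normal in a condensed article. The two-site rule also has a rationale: the inclusion criteria require dissection of the pelvic side walls and/or rectovaginal space, and the Discussion's argument is about separating injured surfaces. The sutures are out by 48 hours and the scan is at three months, so lasting anterior-wall fixation may be rare.

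Much of that stands. The definitions are nested, and a reader who infers two rival primary endpoints goes beyond the text. Treating the Follow-up sentence as shorthand does not remove the problem, however, because the site-limited rule then governs alone. The short suspension makes the harm uncertain but does not exclude it: the Discussion's own rationale is that separation for at least 36 hours affects adhesion formation, and the suspended ovary spends that period at the abdominal wall.

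Three stronger readings are tempting and not supported:

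- **That every uncounted site biases towards suspension.** This follows only for the anterior wall.
- **That the ultrasound validation concerns only fixation to the uterus, a site the rule omits.** One study cited in the Discussion does. Another compared ovarian mobility on ultrasound with laparoscopy (kappa 0.81), and a third is cited whose content is not shown.
- **That the trial will report a false benefit at the rates above.** No document gives a value for q.

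**Conclusion.** The point holds in a limited form. The stated primary outcome rule, read literally, scores an ovary fixed only to the anterior abdominal wall as adhesion-free. Because only the suspended ovary is secured there, any such misclassification favours suspension, against an objective without a site limit.

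The size is conditional. The tabulated false-benefit rates rest on an assumed q, no true any-site difference, independence within a woman and no control-side loss. Smaller q or matching control-side loss brings them down towards nominal. The wording defect does not depend on these figures. As the outcome is written, nothing requires the site of fixation to be recorded, so the trial could not show afterwards whether the problem had occurred.

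**What to change.** Use one per-ovary definition in both Follow-up and Primary outcome measure: adhesion is present if mobility is restricted by fixation to any adjacent structure, including the anterior abdominal wall. Have the blinded operator record the site of fixation at the same three-month scan. Report the side-wall/pouch-of-Douglas version as a secondary outcome, so the mechanism the investigators have in mind is still examined.

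An ovary that cannot be assessed should be recorded as such, by side, and examined in a sensitivity analysis. Scoring an ovary out of reach of the probe as adherent may look like the cautious choice, but nothing in the documents supports it, and it could bias against suspension.

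The cost is a wording change and one extra field on the scan form, with no added visit or procedure. The estimated benefit may be smaller under the any-site definition.

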##### Secondary outcome measures

Secondary outcomes are the presence, intensity and site of post-operative pain.

### Statistical analysis

Women with bilateral endometriosis will receive the normal surgical treatment with the difference that one ovary will be randomised to ovarian suspension and the other to non-suspension. The primary outcome is the binary variable of the presence of ovarian adhesions three months after laparoscopic surgery. The data will be paired binary data.

### Pilot study

A pilot study was conducted to determine the prevalence of ovarian adhesion on transvaginal ultrasound three months after routine laparoscopic treatment of severe pelvic endometriosis (without ovarian suspension).

Between 1st of March 2009 and 1st of September 2009, 16 women post laparoscopic treatment for severe endometriosis were recruited. The mean age was 34.6 years (range 22 to 51). Histology confirmed the diagnosis of endometriosis in all 16 women. Post-operatively, 11/16  (68.8% 95% CI 46.0 to 91.5) women had evidence of ovarian adhesions on TVS. 4/16 (25.0%, 95% CI 3.8 to 46.2) women had unilateral adhesions, while 7/16 (43.8%, 95% CI 19.4 to 68.1) women had adhesions involving both ovaries. The ovarian adhesion rate for each ovary was 18/32 (56.3%, 95% CI 39.1 to 73.4)

### Sample size

The prevalence of ovarian adhesion for each ovary from our pilot study was approximately 60% and this figure was used to calculate the sample size. Clinically significant improvement with ovarian suspension would be defined as a 50% reduction in the prevalence of post-operative ovarian adhesion.

The software provided by Machin et al. was used to calculate the sample size [15]. Assuming two-sided 5% significance and 80% power, 45 women would be required for the study. This calculation assumes that the response to suspension is independent to the response to non-suspension. Allowing for a possible 10% dropout during the follow up period, we plan to recruit 50 patients for the study.

## Discussion

Ovarian adhesions after surgery for pelvic endometriosis are common problems with its associated morbidity. Numerous adhesion prevention strategies, mostly based on microsurgical principles, have been reported. These include minimalising tissue trauma, meticulous hemostasis, irrigation and the use of low reactive sutures. Suspending the ovaries post-operatively has been suggested as an easy and possibly effective way of reducing ovarian adhesions. To the best of our knowledge, a larger prospective study has not been done to evaluate this. Our randomised controlled trial will provide evidence as to whether this simple surgical procedure should be included into the routine surgical treatment of women with severe pelvic endometriosis.

There is a potential risk of injury to the bowels and blood vessels during insertion of the suspension sutures. However, the chance of this occurring is likely to be very small. There has also been no reported complication as a result of ovarian suspension in previous studies.

The original study protocol was to perform a diagnostic laparoscopy to assess for ovarian adhesions three months after surgical treatment for endometriosis. However, due to problems with patient recruitment, the study protocol was modified to the current study.

Traditionally, post-operative adhesions can only be assessed by laparoscopy, but recent studies have shown that targeted palpation with ultrasound probe could be used as an alternative method to diagnose adhesion. Guerriero et al. found that the fixation of the ovary to the uterus evaluated by transvaginal ultrasonography, had a good specificity (86%) and high positive predictive value (PPV) of 81% [16]. More recently, Okaro et al. found good correlation between ovarian mobility on transvaginal ultrasound and at laparoscopy (kappa 0.81) [17]. These positive results were also shared by Holland et al [14]. Transvaginal ultrasound has proven to be an indispensible, non-invasive and inexpensive way of assessing ovarian adhesion.

In our study, a decision was made to perform the post-operative ovarian suspension for 36 to 48 hours. This was different from the duration of suspension of 4 days by Ouahba et al [13]. Our decision was based on an animal study by Harris et al. looking at the kinetics of adhesion formation of injured peritoneal surfaces [18]. They showed that a reduction of adhesion formation is achieved when separation of injured peritoneal surfaces occurs for at least 36 hours. This was in accordance with the duration of hospital stay after laparoscopic surgery for severe endometriosis. Therefore all suspension stitches can be removed before surgical discharge.
